# repeated measurements only if pathologic at baseline

## If the visit is on-site, a rapid SARS-CoV-2 test will be performed at each study visit. If this result is positive, a PCR SARS-CoV-2 test must follow for confirmation.

## 7.2 EFFICACY EVALUATIONS

### 7.2.1 ANTI-dsDNA ANTIBODY TITER ANALYSIS

Given the plasma cell depleting potential of daratumumab, it is hypothesized that the repeated administration of daratumumab may provide a therapeutically relevant reduction of autoreactive PCs in SLE resulting in reduced serum autoantibody levels. Serum anti-dsDNA antibodies will be evaluated using ELISA (ORGENTEC Diagnostika GmbH, Germany).

### 7.2.2 SLE DISEASE ACTIVITY INDEX (SLEDAI-2K)

The SLE Disease Activity Index 2000 (SLEDAI-2K) is an established, validated SLE activity index. It is based on the presence of 24 characteristics in 9 organ systems and measures disease activity in SLE patients over the last 30 days; the index is weighted according to the respective features. The features are scored by the evaluating clinician if they were present within the last 30 days, with more severe features having higher values, and then simply added together to determine the SLEDAI 2K total, which ranges from 0 to 105 [12, 65-67]. The baseline measurement for SLEDAI-2K is defined as the closest measurement taken before baseline administration of the study drug. SLEDAI improvement is defined as a reduction in the overall SLEDAI-2K score from baseline. No worsening of the SLEDAI 2K total score from baseline is defined as a change  $\leq 0$  in the SLEDAI 2K score.

### 7.2.3 SELENA-SLEDAI FLARE INDEX

One key secondary objective is to assess the flare rate in daratumumab treated patients. The corresponding secondary endpoint of this study is the time to first severe flare as measured by the modified SELENA-SLEDAI SLE Flare Index (SFI) [68]. This index categorizes SLE flares as either “mild or moderate” or “severe” based on six variables:

- change in SLEDAI-2K score from most recent assessment to current,
- change in signs or symptoms of disease activity,
- change in prednisone (or equivalent) dose,
- use of new medication for disease activity or hospitalization,
- change in PGA score,
- hospitalization for SLE activity (severe flare only).

The modified SELENA-SLEDAI SFI requires that a patient who has a SLEDAI score  $>12$  is considered as having a severe flare only if they have one other component present. This modification was made

because participants entering the trial with high disease activity (i.e.  $\geq 11$ ) could too easily trigger a severe flare by minor increases in SLEDAI score.

Lupus flares should be treated primarily with medications listed in the section 6.5 RESCUE MEDICATION. Only in case of insufficient response to such therapies and presence of severe SLE organ manifestations, medications listed in section 6.6 PROHIBITED MEDICATION can be used. In this situation, the participant will be considered as treatment failure but will not need to be withdrawn from the study (see section 8.2 DISCONTINUATION OF STUDY TREATMENT). To ensure that the interpretability of SLE FLARE INDEX will not be impacted by prohibited medication, such patients will be included in the intention-to-treat analysis set (see section 9.3. ANALYSIS SETS), similar to patients with a dose interruption in case of adverse events.

#### 7.2.4 BRITISH ISLES ASSESSMENT GROUP (BILAG)

The British Isles Assessment Group (BILAG) index scores patients based on the need for alterations or intensification of therapy [13, 69]. The assessing physician will evaluate 97 items divided into 9 organ system domains. The physician considers presence of each item in the past 4 weeks and answers by using the following options:

- 0=not present,
- 1=improving,
- 2=same,
- 3=worse, or
- 4=new.

Each organ/system domain is classified as BILAG A, B, C, D, or E based upon criteria specific to the domain [13]. The BILAG index was designed to give practicing physicians a tool to help indecision-making based on amount of activity in each organ/system. The baseline measurement for the BILAG is defined as the closest measurement taken during the study and prior to administration of study agent at Week 0.

- BILAG Improvement is defined as (1) all BILAG A scores at baseline improved to either B, C or D and (2) all BILAG B scores at baseline improved to C or D and (3) no worsening in disease activity defined as no new BILAG A scores and  $\leq 1$  new BILAG B score.
- Major Clinical Response in BILAG is defined as BILAG C score or better in all organ domains.
- No worsening in BILAG disease activity is defined as no new BILAG A scores and  $\leq 1$  new BILAG B score.

#### 7.2.5 CUTANEOUS LUPUS ERYTHEMATOSUS DISEASE AREA AND ACTIVITY INDEX (CLASI)

The activity and severity of cutaneous lupus disease are measured by the Cutaneous Lupus Erythematosus Disease Area and Severity Index (CLASI). The CLASI is a diagnostic instrument for assessing disease activity and skin damage in patients with cutaneous lupus erythematosus with or without systemic involvement [70]. The CLASI is based on two scores; the first summarizes the activity of the disease, while the second is a measure of the damage caused by the disease (CLASI Activity and CLASI Damage Scores). The SLE activity is evaluated by the clinician on the basis of erythema, scale/hyperkeratosis, mucous membrane involvement, acute hair loss and non-scarring alopecia. The damage is evaluated in terms of dyspigmentation and scarring, including scarring alopecia. The scores are calculated by simple addition based on the extent of the symptoms [70]. CLASI scores are ranging from 0-70 for activity and 0-56 for damage, with higher scores indicating a worse disease activity.

### 7.2.6 CDAI

The CDAI (Clinical Disease Activity Index) is a validated clinical composite score to determine the disease activity in patients with rheumatoid arthritis. The CDAI score will be calculated at each assessment time point.

The components of the CDAI include:

- Tender/Painful Joint Count (28)
- Swollen Joint Count (28)
- Patient's Global Assessment (PGA) of Arthritis (Numeric Rating Scale [NRS] 1-10)
- Evaluator Global Assessment (EGA) of Arthritis (NRS 1-10)

The CDAI is a sum score of each variable as follows: SJC (28) + TJC (28) + PGA + EGA.

Interpretation of the score for rheumatoid arthritis:

Remission, CDAI  $\leq 2.8$ ; Low Disease Activity, CDAI  $> 2.8$  and  $\leq 10$ ; Moderate Disease Activity, CDAI  $> 10$  and  $\leq 22$ ; High Disease Activity, CDAI  $> 22$ .

### 7.2.7 SERUM ANALYSES

In serum samples, lupus related variables, such as complement factors for C3 and C4 and autoantibodies, including level and specificity of antinuclear antibodies (ANA), and potentially present antiphospholipid antibodies (cardiolipin, beta2-glycoprotein and anti-phosphatidyl antibodies) will be investigated. In addition, vaccine titers will be analyzed, including Tetanus toxoid, Diphtheria and Measles titers. Furthermore, serum titer for immunoglobulins (IgM, IgA, IgG) will be investigated.

### 7.2.8 SHORT FORM 36 (SF-36)

The 36-point questionnaire Short-form Health Survey (SF-36) is a patient reported outcome (PRO) questionnaire to measure Health Related Quality of Life (HRQoL), which comprises 36 items in 8 areas covering a range of the following topics:

- Physical function limitations
- Restrictions for common role activities
- Physical pain
- General mental health (mental stress and well-being)
- Vitality (energy and fatigue)
- Restrictions in social functioning due to physical or mental health problems
- Restrictions in usual role activities due to personal or emotional problems
- General health perception

The standard version uses a 4-week recall period and 5-point Likert response options ranging from "Excellent" to "Poor" (except the General Health item, which uses a one-year recall period, and Likert response options ranging from "Much Better" to "Much Worse"). The evaluation results in a physical component score (PCS) score and a mental component score (MCS) score as well as 8 subscale scores. The scale scores and the summary scores are converted to 0-100 using a standards-based system, with linear transformations being performed to transform the scores to a mean of 50 and standard deviations of 10 based on general U.S. population standards. Higher scores represent better results. SF-36 can be completed in 5 to 10 minutes. The instrument has undergone extensive linguistic and cultural validation.

The concepts measured with SF-36 are not specific to a particular age, disease, or treatment group, allowing a comparison of the relative burden of different diseases and the benefits of different treatments. A change of 2.5 points in any of the subscales or 5 points for component evaluation is associated with a clinically significant change [71-74].

### 7.2.9 PHYSICIAN'S GLOBAL ASSESSMENT OF DISEASE ACTIVITY

The physician's global assessment of disease activity (PGA) will be assessed independent of subject's assessment on a visual analogue scale (VAS) with responses ranging from 0-3, and verbal anchors "*No Lupus Activity*" (0) on the far-left side of the scale and "*Extremely Active Lupus*" (3) on the far right of the scale. Disease activity can range from 0 representing no disease activity, 1 representing mild disease activity, 2 representing moderate disease activity, to 3 representing extremely active disease [75, 76].

### 7.2.10 FACIT FATIGUE QUESTIONNAIRE

The Functional Assessment of Chronic Illness Therapy - Fatigue Scale (FACIT-Fatigue) version 4.0 is a 13-item questionnaire that is formatted for self-administration and measures patient-reported fatigue and its impact on daily activities and functions over the past seven days. Subjects are asked to answer each question using a 5-point Likert scale with the following response options.

- 0 = not at all
- 1 = a little bit
- 2 = somewhat
- 3 = quite a bit
- 4 = very much

The interpretation of the FACIT fatigue results is defined as a higher value indicating lower fatigue, with a possible range of values from 0-52, where 0 is the worst and 52 is the best possible value [77]. The FACIT-F Scale has been validated in patients with SLE [78, 79].

## 7.3 EFFICACY ENDPOINT DEFINITIONS

### 7.3.1 REDUCTION OF Anti-ds-DNA ANTIBODIES IN SERUM

To determine the primary endpoint, anti-dsDNA antibody titers in patient's serum will be assessed 4 weeks after the last daratumumab injection and compared to baseline level.

### 7.3.2 LUPUS LOW DISEASE ACTIVITY STATE

In this study the following version of LLDAS is used and is defined as meeting all the following conditions [80]:

Disease activity:

- SLEDAI-2K  $\leq 4$ , with no activity in major organ systems (renal, CNS, cardiopulmonary, Vasculitis, fever), and no hemolytic anemia, or gastrointestinal activity
- No new features of lupus disease activity compared with the previous assessment  
SELENA-SLEDAI PGA score of  $\leq 1$  on a 0-3 scale VAS.

Immunosuppressive medications:

- A current prednisone (or equivalent) dose of  $\leq 7.5$  mg daily
- Well-tolerated standard maintenance doses of permitted immunosuppressive drugs and approved biological agents.

### 7.3.3 SLE RESPONDER INDEX (SRI-4)

The SRI-4 response is defined as  $\geq 4$ -point reduction from baseline in SLEDAI-2K score, no new BILAG A and no more than 1 new BILAG B domain score, and no worsening from baseline in the PGA ( $< 10\%$  worsening from baseline) [65]. For the endpoint analysis in this study, SRI-4 composite response is the proportion of subjects who achieve a SLEDAI-2K SRI-4 response at Week 3, 5, 7, 9, 12, 16, 20, 24, 28, 32, 36 of the core study period, and at Week 42, 48, 54, 60, 66, 72, 78 and 84 of the LTE observational period.

### 7.3.4 SLE FLARE INDEX

For this study, SLE flares will be defined as follows:

SLEDAI-2K flare is defined as at least 1 new SLEDAI-2K mild/moderate or severe flare compared with baseline as assessed using the SLEDAI flare index (SFI).

Severe SLEDAI-2K flare is defined as presence of one or more of the following:

- Increase in SLEDAI-2K score to greater than 12. If this is the only criteria met, at least one additional criterion below must also be present to be considered a severe SLEDAI-2K flare
- New/Worse SLE activity (CNS, vasculitis, nephritis, myositis, thrombocytopenia ( $< 60,000/\text{mm}^3$ ), hemolytic anemia (hemoglobin  $< 7$  g/dL or decrease in hemoglobin  $> 3$  g/dL) requiring one or more of the following: (1) increase in prednisone (or equivalent) dose to  $> 0.5$  mg/kg/day, (2) a doubling or greater of prednisone (or equivalent) dose, (3) addition of a new systemic immunosuppressant agent (cyclophosphamide, AZA, MTX, MMF, belimumab, rituximab, or other systemic immunosuppressant therapy), or (4) hospitalization for SLE activity
- Increase in prednisone (or equivalent) to  $> 0.5$  mg/kg/day for SLE activity
- New cyclophosphamide, AZA, MTX, MMF, belimumab, rituximab (or other systemic immunosuppressant therapy) for SLE activity
- Hospitalization for SLE activity
- Increase in the 0-3 VAS anchored PGA score to  $> 2.5$

Mild/moderate SLEDAI-2K flare is defined as presence of one or more of the following:

- Increase in SLEDAI-2K score of 3 points or more (but not to more than 12)
- New/worse SLE activity (discoid, photosensitive, profundus, cutaneous vasculitis, bullous lupus, nasopharyngeal ulcers, pleuritis, pericarditis, arthritis, fever due to SLE)
- Increase in prednisone (or equivalent), but not to  $> 0.5$  mg/kg/day, for SLE activity
- Added NSAID or hydroxychloroquine (or other antimalarial therapy) for SLE activity
- Increase in the 0-3 VAS anchored PGA score by  $\geq 1$ , but not to more than 2.5

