### 6.5 RESCUE MEDICATION

For the treatment of disease flares, defined according to the SLEDAI-flare index (SFI), administration of glucocorticoids is allowed up to a maximum dose of 100mg/day. In case of recurring flares or ongoing disease activity, defined as a state of not achieving low disease-activity (LLDAS), administration of additional disease-modifying drugs is allowed from Week 12 (primary endpoint visit) (except for medications listed in section 6.6 PROHIBITED THERAPIES).

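### The flare definition in section 7.3.4 leaves a SLEDAI-2K rise to more than 12 ungraded when no other criterion is met, although a smaller rise counts as a flare

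*Protocol*

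**What the plan says.** Section 7.3.4 sets the flare definition for this study and allows two grades: "SLEDAI-2K flare is defined as at least 1 new SLEDAI-2K mild/moderate or severe flare compared with baseline".

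- **Severe, score item:** a SLEDAI-2K increase to more than 12, with the condition "If this is the only criteria met, at least one additional criterion below must also be present to be considered a severe SLEDAI-2K flare".
- **Mild/moderate, score item:** "Increase in SLEDAI-2K score of 3 points or more (but not to more than 12".
- **Mild/moderate, other items:** new or worse activity from a fixed list ("discoid, photosensitive, profundus, cutaneous vasculitis, bullous lupus, nasopharyngeal ulcers, pleuritis, pericarditis, arthritis, fever due to SLE"), a limited prednisone increase, an added NSAID or antimalarial, or a PGA rise of at least 1 that does not exceed 2.5.

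Section 7.2.3 describes the same change to the severe grade. A patient with a score above 12 "is considered as having a severe flare only if they have one other component present". The reason given is that patients entering with high activity "could too easily trigger a severe flare by minor increases in SLEDAI score". Section 3.2.3 repeats that severe flares triggered only by the score are excluded. No section says where those events go instead.

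Section 3.2.3 lists time to first flare, with both grades, as a secondary endpoint through Week 84. Section 9.5.2 analyses time to flare by Kaplan-Meier. Section 7.2.3 names time to first severe flare as the endpoint. Section 6.5 uses the index for rescue: "For the treatment of disease flares, defined according to the SLEDAI-flare index (SFI), administration of glucocorticoids is allowed".

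**The concern.** The cap at 12 in the mild/moderate item fits an index in which any rise above 12 is already severe. The protocol changed the severe rule and left the cap in place. A rise past 12 with nothing else then drops out of both grades, so the event definition is not monotone: a small worsening is an event and a larger one may not be.

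For time to first flare the error runs one way. Qualifying worsening is missed, or is dated later when some other criterion is met. It arises most easily at higher reference scores, and entry requires a SLEDAI-2K of at least 6. The same definition carries over into section 6.5.

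**Working it through.** The protocol states no figure to reproduce; this is a check of the definition's logic.

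**Inputs.** Score rules from section 7.3.4, item weights from the SLEDAI-2K form in attachment B, entry score of at least 6 from section 5.1.

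**Rules.** Let s be the reference score and d the rise, with no other criterion met.

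- Severe needs s + d > 12 and another criterion, so it is never met here.
- Mild/moderate needs d ≥ 3 and s + d ≤ 12, that is 3 ≤ d ≤ 12 − s.

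| Reference score s | Largest counted rise, 12 − s | Rises that count by score alone | Rises of 3 or more that do not |
|---|---|---|---|
| 6 | 6 | 3 to 6 | 7 or more |
| 8 | 4 | 3 to 4 | 5 or more |
| 9 | 3 | exactly 3 | 4 or more |
| 10 | 2 | none (10 + 3 = 13) | all |
| above 10 | below 2 | none | all |

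So 6 to 9 and 6 to 12 are flares and 6 to 14 is not; 9 to 12 is a flare and 9 to 13 is not. A score-based route to any flare exists only from 9 or below.

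**Example with items that trigger neither list on their own.** Start at 6.

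- New low complement (2) and leukopenia (1): 6 + 3 = 9, a mild/moderate flare.
- New hematuria (4) and proteinuria (4): 6 + 8 = 14, no flare unless treatment changes, the patient is hospitalised or PGA rises enough. Nephritis is named only on the severe list, and there only when it requires escalated treatment or hospitalisation.

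**What is still captured.** A rise past 12 counts as a flare if it comes with a manifestation on the mild/moderate list, a treatment increase for SLE activity, hospitalisation or a qualifying PGA rise.

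**Reference visit.** Section 7.3.4 compares with baseline; section 7.2.3 uses the most recent assessment. The table holds for either, since s is whichever score is used.

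**After the repair.** If a rise of 3 or more that is not severe counts as mild/moderate, then 6 to 14, 9 to 13 and 10 to 13 all become mild/moderate. A two-point rise from 11 to 13 with nothing else remains no flare.

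**The case against.** **The exclusion is deliberate.** True for the severe grade, and section 7.2.3 explains it. The explanation concerns severe flares only and gives no reason for removing these rises from flares altogether.

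**Section 7.2.3 names time to first severe flare as the endpoint, which the gap cannot touch.** This stands. The effect is confined to the wording in sections 3.2.3 and 9.5.2, and the two endpoint wordings conflict.

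**Section 7.2.3 asks for one other component, after a list that includes a change in signs or symptoms.** On that reading the hematuria and proteinuria example is arguably severe rather than ungraded. This also stands in part: the example rests on section 7.3.4, which presents itself as the study's definition. A rise past 12 that meets no other criterion is ungraded under either wording.

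**Worsening shows elsewhere.** SLEDAI-2K change, SRI-4, LLDAS, PGA, urinary protein/creatinine ratio and time to new treatments are also reported. The study is exploratory, with 10 patients and no confirmatory test of the primary change. This limits the consequence.

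**Rescue does not depend wholly on the flare grade.** From Week 12, section 6.5 also allows added disease-modifying drugs when LLDAS is not achieved, and a score above 12 fails its limit of 4. Only the glucocorticoid sentence is tied to the index. Before Week 12, though, that sentence, the stable-dose rule in section 6.4.1 and the flare item for a prednisone increase are partly circular: the increase would create the flare that permits it.

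**Stronger readings.** A reader might infer that large relapses in general go unscored, that durability is overstated in the sickest patients, or that the flare rate is off by 10 percentage points (1/10) per missed event. The protocol does not support these. Most listed forms of worsening are still caught, some events would only be delayed, and nothing shows that any event would be missed.

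**Conclusion.** The definition is wrong as written. With two grades, a score item barred from severe when it stands alone, and a mild/moderate item capped at 12, a SLEDAI-2K rise to more than 12 that meets no other criterion has no grade, while a smaller rise of at least 3 points to 12 or less is a flare. In score terms the gap starts at a rise of 7 from a reference of 6, at 4 from a reference of 9, and covers every rise of 3 or more from 10 upward.

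This rests on section 7.3.4 governing and on no other criterion being met. The frequency is unknown, so no effect on the Kaplan-Meier estimate can be stated. Severity is minor to moderate: one descriptive secondary endpoint is affected, and the repair is simple.

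**What to change.** In section 7.3.4, reword the mild/moderate score item to: *Increase in SLEDAI-2K of 3 points or more that does not meet the definition of a severe flare.* This keeps the intended change to the severe grade and grades the orphaned rises as mild/moderate. If excluding them from all flares is intended, state that and give the reason.

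In the same amendment:

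- Align sections 3.2.3, 7.2.3 and 7.3.4 on whether the endpoint is first flare or first severe flare.
- Choose between the wider wording in section 7.2.3 ("is considered as having a severe flare only if they have one other component present") and that in section 7.3.4 ("at least one additional criterion below must also be present to be considered a severe SLEDAI-2K flare"), and say which list the further criterion may come from.
- Fix the reference visit as baseline or most recent assessment.
- Reconcile section 6.5 with section 7.3.4, since rescue glucocorticoids are tied to the index. No clinical rule is proposed here.

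The cost is one reworded item, the alignment edits and the flare programming. No new data are needed. The reported flare rate may be somewhat higher.

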### 7.3.5 BILAG Response

BILAG Improvement is defined as (1) all BILAG A scores at baseline improved to either B, C or D and (2) all BILAG B scores at baseline improved to C or D and (3) no worsening in disease activity defined as no new BILAG A scores and  $\leq 1$  new BILAG B score. Major Clinical Response in BILAG is defined as BILAG C score or better in all organ domains. No worsening in BILAG disease activity is defined as no new BILAG A scores and  $\leq 1$  new BILAG B score.

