## 5.1 INCLUSION CRITERIA OF THE CORE STUDY PERIOD

Each potential participant must satisfy all the following criteria to be enrolled in the study:

1. diagnosis of SLE according to the 2019 EULAR/ACR Systemic Lupus Erythematosus classification criteria.
2. age between 18 and 60 years, inclusive, at consent.
3. have a body mass index (BMI) between 18 and 32 kg/m^2 (BMI = weight/height), inclusive, and a body weight of no less than 35 kg.
4. demonstrate moderate to severe disease based on SLEDAI-2K score  $\geq 6$  observed at screening
5. SLEDAI-2K  $\geq 4$  for clinical features (i.e. SLEDAI excluding laboratory results) at screening
6. have a positive anti-double stranded deoxyribonucleic acid (anti-dsDNA) test, as measured by enzyme-linked immunosorbent assay (ELISA) test.
7. Failure or lack of tolerability of at least 2 previous state-of-the-art immunosuppressive drugs/immunomodulatory drugs including antimalarials (does not account for glucocorticoids).
8. if using oral corticosteroids, must be receiving this medication for at least 4 weeks and on a stable dose equivalent to an average dose of  $<20$  mg of prednisone daily for at least 4 weeks prior to the first dose of study agent.
9. if using immunosuppressive drugs within the past 6 months, must not have exceeded the following dose levels: methotrexate 25 mg/week, azathioprine 2mg/kg/day, mycophenolate mofetil (MMF) 3g/day, or mycophenolic acid (MPA) 1440mg/day.
10. if using immunosuppressive drugs, must be using not more than 1 immunosuppressive drug (does not account for antimalarials and glucocorticoids) and not have used any additional immunosuppressive drug within the past 3 months prior to the first dose of study agent.
11. must have laboratory test results within the following parameters:
  - a. Hemoglobin  $\geq 8.0$  g/dL (SI:  $\geq 80$  g/L)
  - b. White Blood Cells  $\geq 3.0 \times 10^3/\mu\text{L}$  (SI:  $\geq 3.0$  GI/L)
  - c. Neutrophils  $\geq 1.5 \times 10^3/\mu\text{L}$  (SI:  $\geq 1.5$  GI/L)
  - d. Platelets  $\geq 100 \times 10^3/\mu\text{L}$  (SI:  $\geq 100$  GI/L)
  - e. Serum creatinine  $\leq 2.0$  mg/dL (SI:  $\leq 177$   $\mu\text{mol/L}$ )
  - f. aspartate aminotransferase (AST) and alanine aminotransferase (ALT) levels must be within 2 x ULN range
12. must sign an informed consent form (ICF), indicating that he or she understands the purpose of, and procedures required for, the study and is willing to participate in the study.

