|------------------------------|------------------------------------------------------------------------------------------------------------------------|---|--------------------------|
| Proteinuria           | New onset or recent increase of more than 0,5mg/24hours.                                                               | 4 |  |
| Pyuria                | > 5 white blood cells/high field. Exclude infection.                                                                   | 4 |  |
| Rash                  | Ongoing inflammatory lupus rash.                                                                                       | 2 |  |
| Alopecia              | Ongoing abnormal, patchy or diffuse loss of hair.                                                                      | 2 |  |
| Mucosal ulcers        | Ongoing oral or nasal ulcerations.                                                                                     | 2 |  |
| Pleurisy              | Pleuritic chest pain with pleural rub or effusion, or pleural thickening.                                              | 2 |  |
| Pericarditis          | Pericardial pain with at least 1 of the following: rub, effusion, or electrocardiogram or echocardiogram confirmation. | 2 |  |
| Low complement        | Decrease in CH50, C3, or C4 below the lower limit of normal for testing laboratory.                                    | 2 |  |
| Increased DNA binding | Increased DNA binding by Farr assay above normal range for testing laboratory.                                         | 2 |  |
| Fever                 | >38°C. Exclude exclude infectious cause.                                                                               | 1 |  |
| Thrombopenia          | <100,000 platelets / x 10  /L, exclude drug causes                                                         | 1 |  |
| Leukopenia            | <3,000 white blood cells / x 10  /L, exclude drug causes                                                   | 1 |  |

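### BILAG Improvement and Major Clinical Response need no BILAG A or B at baseline, so an unchanged patient without either counts as a responder

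*Protocol*

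**What the plan says.** Section 7.2.4 explains the scale: "Each organ/system domain is classified as BILAG A, B, C, D, or E based upon criteria specific to the domain". Sections 7.2.4 and 7.3.5 then give the same three response categories.

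- **BILAG Improvement** has three conditions. The first is in "BILAG Improvement is defined as (1) all BILAG A scores at baseline improved to either B, C or D". The second is "2) all BILAG B scores at baseline improved to C or D". The third begins "3) no worsening in disease activity defined as no new BILAG A scores and" and goes on to allow at most one new B.
- **Major Clinical Response**: "Major Clinical Response in BILAG is defined as BILAG C score or better in all organ domains".
- **No worsening**: no new A and at most one new B, which is the third condition of Improvement standing alone.

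On entry, section 5.1 asks patients to "demonstrate moderate to severe disease based on SLEDAI-2K score" of at least 6, and for a score of at least 4 "for clinical features (i.e. SLEDAI excluding laboratory results) at screening". No inclusion criterion mentions BILAG. Section 9.1.1 tabulates the number of baseline BILAG A or B scores, but no section uses that count to restrict who is assessed for response.

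**The concern.** The first two conditions of Improvement test only A and B scores that exist at baseline. If a patient has none, they have nothing to test and are met by default. What remains is the no-worsening condition, so a category labelled improvement records only that the patient did not get clearly worse. Because one new B is tolerated, it also accepts a patient who moved from no A or B to one B, which is a deterioration. Major Clinical Response describes a state at follow-up, not a change, so a patient already in that state at baseline meets it with no change at all.

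The two responses are defined under section 7.3, the efficacy endpoint definitions, and section 9.5.2 reports clinical efficacy parameters descriptively at each assessment. In an uncontrolled trial of 10 patients, a count obtained this way has no comparator to show how much of it arose by default.

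**Working it through.** The protocol states no figure for BILAG response, so there is none to reproduce. The check is logical, followed by simple arithmetic.

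**Step 1: the rules written out.** The inputs are sections 7.2.4 and 7.3.5, with 9 organ domains. A new A is an A where the baseline was not A. A new B is a B where the baseline was C, D or E.

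- Improvement = (every baseline A is now B, C or D) and (every baseline B is now C or D) and (new A = 0 and new B ≤ 1)
- Major Clinical Response = (every domain is now C or better)
- No worsening = (new A = 0 and new B ≤ 1)

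**Step 2: single cases.**

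| Baseline | Follow-up | Improvement | Major Clinical Response |
|---|---|---|---|
| no A or B | unchanged | yes | yes |
| no A or B | one new B | yes | no |
| no A or B | two new B | no | no |
| no A or B | one new A | no | no |
| one B | unchanged | no | no |

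**Step 3: all follow-up patterns for one baseline without A or B** (three domains at C, six at D). Allowing A to D in each domain gives 4^9 = 262,144 patterns. Those with no A and no B number 2^9 = 512. Those with no A and exactly one B number 9 × 2^8 = 2,304. Improvement is met in 512 + 2,304 = 2,816 patterns, and so is no worsening. The two rules agree in all 262,144. Major Clinical Response is met in the 512 patterns with no A and no B.

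**Step 4: do the entry criteria exclude such patients?** On the SLEDAI-2K form in the attachments, rash ("Ongoing inflammatory lupus rash") scores 2 and alopecia scores 2, so the clinical part is 2 + 2 = 4. One serological item (DNA binding or low complement) adds 2, giving a total of 6. Both thresholds in 5.1 can thus be met with skin and hair items alone, and the BILAG form lists mild grades for skin eruption and alopecia. This shows that section 5.1 contains no barrier. It does not show which BILAG letter such a patient would receive.

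**Step 5: size.** With all 10 enrolled patients in the denominator (9.3), one patient who meets the rule by default contributes 1/10 = 10 percentage points. The number of such patients, k, is not in the protocol. For assumed k = 1, 2 or 3 the contribution is 10, 20 or 30 percentage points.

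**Step 6: effect of the change.** Let r be the number improved among the 10 − k patients with a baseline A or B, and suppose the k others stay unchanged. As written the proportion is (r + k)/10. With the restricted denominator it is r/(10 − k). With the others counted as not improved it is r/10. With r = 0 and k = 2, these are 20%, 0% and 0%.

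**The case against.** The strongest reply is that little depends on these categories. BILAG Improvement and Major Clinical Response appear neither among the secondary endpoints in 3.2.3 nor in the synopsis, and the objectives of the extension period do not name them. BILAG enters a listed endpoint only through the no-worsening part of SRI-4, where tolerating one new B is part of the definition and a SLEDAI fall of at least 4 points is also required. A default BILAG response therefore cannot create an SRI-4 responder. The primary endpoint is anti-dsDNA. All of this stands and limits the reach of the point.

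A second reply is that the frequency cannot be seen. Domain grades follow scoring rules and a glossary that are not in the protocol, and the population has moderate to severe disease after failure or intolerance of at least two drugs. This also stands: the number of affected patients is an assumption.

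A third reply is that asking for all baseline A scores to improve presupposes a score to improve, and that the evaluable denominator can be left to the analysis plan. This helps only in part. The protocol fixes the rule itself, and applied as written it gives the results in the table. Major Clinical Response does not mention baseline, so the charitable reading does not reach it.

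A reader might infer more than the text supports, for example that every patient without a baseline A or B is automatically improved, that one new B satisfies both rules, or that unchanged patients in general count as improved. The table rules out all three. A new A or two new Bs fails Improvement, one new B fails Major Clinical Response, and an unchanged patient with a baseline B is not a responder.

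**Conclusion.** The point holds as a defect in two definitions. For a patient with no baseline A or B, BILAG Improvement is identical to the protocol's own no-worsening category, and an unchanged patient of this kind also meets Major Clinical Response. Nothing in 5.1 keeps such patients out, and no section restricts the denominator.

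The size is 10 percentage points for each such patient who meets the rule, with all 10 patients in the denominator. It is tempting to conclude that the trial's BILAG response will be substantially inflated, but the protocol does not support that, because it gives neither the share of patients without a baseline A or B nor the grading rules needed to estimate it. The listed efficacy endpoints, including SRI-4 and the primary endpoint, are unaffected. The correction is still worth making, because the rule as written puts unchanged patients, and some who have worsened, under the label of improvement.

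**What to change.** In sections 7.2.4 and 7.3.5, state that BILAG Improvement and Major Clinical Response are evaluated only in patients with at least one BILAG A or B at baseline, and report that denominator with each proportion. Report patients without a baseline A or B only under the no-worsening category. Alternatively, keep all patients in the denominator and count those without a baseline A or B as not improved.

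The restriction does not remove the tolerance of one new B for the remaining patients: a baseline B that falls to C with a new B in another domain would still count as improved. One added sentence should say whether that is intended.

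No new data are needed, since BILAG is already scored at baseline and 9.1.1 already tabulates the A and B counts. The cost is a wording change in two sections and either a smaller denominator or a less favourable response proportion.
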